## Abstract

**Background:**

Postpartum haemorrhage (PPH) is a major cause of maternal morbidity. Bleeding is caused by a combination of physical causes, such as failure of the uterus to contract or operations, and is made worse by impairment of the blood clotting system. A number of studies have shown that low levels of the blood clotting factor fibrinogen are associated with progression of bleeding, the need for invasive interventions and transfusions of red blood cells and fresh frozen plasma (FFP). This trial will investigate whether early infusion of fibrinogen concentrate during a major PPH, with the aim of correcting a low fibrinogen to a level that is normal for delivery, based on the Fibtem test, reduces the total number of allogeneic blood products (red blood cells, FFP, cryoprecipitate and platelets) transfused after study medication until discharge, compared to placebo.

**Methods/design:**

This is a prospective, randomised, double-blind placebo controlled trial. Women will enter an observational phase and if their Fibtem levels fall they will be randomised in the interventional phase. A total of 60 women will be randomised and women are eligible for the trial if they meet all of the following inclusion criteria: age 18 years or over, gestation ≥24 + 0 weeks, haemorrhage of about 1500 ml and on-going bleeding without another complication or haemorrhage of about 1000 ml and caesarean section/uterine atony/placental abruption/placenta praevia/cardiovascular instability or microvascular oozing. Participants with a Fibtem A5 < 16 mm will be randomly allocated to receive either a bolus infusion of fibrinogen concentrate or placebo (isotonic saline). The dose of fibrinogen concentrate or placebo will be calculated based on the woman’s ideal body weight for height and the measured Fibtem A5 with the aim of increasing the Fibtem A5 to 23 mm.

**Discussion:**

The trial aims to provide evidence on the efficacy and safety of fibrinogen concentrate during acute bleeding in an obstetric setting.

**Trial registration:**

ISRCTN ref: ISRCTN46295339 (01.07.2013); EudraCT: 2012-005511-11 (28.11.2012), UKCRN ref: 13940.

## Background

Postpartum haemorrhage (PPH) is defined as blood loss of ≥500 ml after vaginal delivery or ≥1000 ml after caesarean section. Major PPH can be divided into moderate at 1000–2000 ml or severe at over 2000 ml. Severe PPH is also defined as a fall in haemoglobin of ≥40 g/l or the need for transfusion of 4 or more units of red blood cells (RBC) [1]. Massive PPH has been described as bleeds of more than 2500 ml and is associated with significant morbidity, even in resource-rich countries, including admission to high dependency and intensive care and emergency hysterectomy (6-8% of cases) [2].

PPH is a major cause of maternal morbidity and mortality. Worldwide PPH accounts for at least 30% of all maternal deaths [3], whilst in the UK massive PPH accounts for 75% of severe childbirth-related morbidity affecting 6:1000 deliveries each year [2]. The incidence of massive PPH has increased over the last 10 years in the UK and other countries [2,4-6] and outcomes have not improved over that time period. Deaths directly caused by obstetric bleeding in the UK have had an incidence between 0.33 and 0.93 per 100,000 deliveries over the last 15 years [7].

PPH results from a combination of physical causes such as trauma, uterine atony and placental complications and is exacerbated by haemostatic impairment. Haemostatic impairment is caused by a combination of consumptive and dilutional coagulopathies. This leads to low levels of fibrinogen early during PPH and before clinically significant depletion of other coagulation factors [8]. The low fibrinogen level results in the formation of poor quality clots and contributes to on-going bleeding. Bleeding is exacerbated by fibrinolysis (the breakdown of fibrin clots), which is often increased during PPH.

There are no high-quality data to guide the replacement of coagulation factors during PPH. Coagulation factors are often replaced with fresh frozen plasma (FFP) but there is limited evidence to support its efficacy. When as well as how much FFP to infuse in any clinical situation is debated [9]. Current guidelines recommend identical haemostatic support during PPH as for all other clinical situations of massive haemorrhage [1,10,11]. There is limited evidence to support these transfusion guidelines in any clinical situation and none in PPH; studies in this area have been highlighted as a priority [12].

Physiological changes in coagulation at the time of delivery mean that standard transfusion triggers, such as those used in trauma (and recommended in current guidelines), are unlikely to be applicable at the time of a major PPH. At term the prothrombin time (PT) and activated partial thromboplastin time (aPTT) are shorter and fibrinogen is higher than in the non-pregnant population. In addition, the PT and aPTT often remain normal despite very large bleeds. The current recommendation is to infuse FFP during PPH when the PT or aPTT is greater than 1.5 times normal [1], but this is not supported by any evidence and these coagulation abnormalities will be associated with established haemostatic failure and microvascular bleeding [11]. Audit data demonstrate that clinicians often do not follow these recommendations in clinical practice when dealing with severe PPH [8].

The fibrinogen level at the time of delivery is between 4–6 g/l compared to 1.5-4 g/l in the non-pregnant healthy population. Current recommendations are to maintain the fibrinogen level above 1 or 1.5 g/l [1,10,11]. During an on-going PPH it is not known whether fibrinogen should be replaced to a level appropriate to the non-pregnant population or a level appropriate for the time of delivery. There are data, however, suggesting that a fibrinogen level associated with the time of delivery might be more appropriate.

There are no systematic reviews of the use of fibrinogen concentrate in PPH; however, the fibrinogen level has been shown to be a useful predictor of progression from early to severe PPH in multiple studies. A fibrinogen level below 2.9 g/l, taken early during labour (before any bleeding has occurred), had an odds ratio of 19 for progression to PPH. In this study a fibrinogen of <2.9 g/l had a positive predictive value (PPV) of 39% for progression to PPH whilst a fibrinogen above 2.9 g/l had a negative predictive value (NPV) of 94% [13]. In other studies, a low fibrinogen level, taken early during a PPH, was predictive of the need for invasive procedures or infusion of RBC and FFP [14-16]. Charbit et al. found that a fibrinogen level below 2 g/l, taken during an on-going PPH, had a PPV of 100% for progression to severe PPH, defined in part as the need for at least 4 units of RBC, whilst a fibrinogen level above 4 g/l had a NPV of 85-90% [14]. Gayat et al. demonstrated that a fibrinogen level below 2 g/l, taken after a 1000 ml estimated blood loss, was an independent predictor for the need for an invasive procedure [15].

Retrospective data from 240 women experiencing a major PPH in a 6-month period, taken from the Cardiff Maternity Database, also found that fibrinogen was a useful predictor for progression to the need for RBC transfusion. The receiver-operator characteristic curve (ROC) area under the curve (AUC) (95% CI) for any RBC transfusion was 0.78 (0.74-0.83), the need for 4 units of RBC 0.8 (0.73-0.86) and for progression to 2500 ml blood loss 0.85 (0.78-0.93). In women with a fibrinogen level less than 3 g/l, 18/21 (86%) required RBC transfusion (median 3 units range 0–12) and 11 also required FFP. The mean (SD) allogeneic units (RBC + FFP + cryoprecipitate + platelets) infused was 5.8 (6.8). In contrast, in women with a fibrinogen level greater than 4 g/l (a normal level for delivery) 7/81 (8.6%) required RBC transfusion, a mean (SD) of 0.2 (0.6) units/woman, and none required FFP. These data have been confirmed in a prospective, consecutive cohort of 346 women in Cardiff experiencing a major PPH that showed that the ROC AUC (95% CI) for fibrinogen (*n* = 332) as a predictive biomarker for the need for 4 or more units of RBC transfusion was 0.77 (0.66-0.87).

Bleeding during PPH is often very fast and, in order to reduce the risk of progression from moderate to massive PPH, early intervention is required. If a low fibrinogen level is to be used as a trigger for intervention the result needs to be available to the clinician as soon as possible. Testing fibrinogen in the laboratory takes between 60 to 90 min and this is too long to be clinically useful in most cases of PPH. Furthermore, during a PPH the fibrinogen level may fall rapidly and so repeated measurements may be required to identify when a critically low level has been reached. A better strategy would be to use point-of-care testing to trigger a fibrinogen replacement and to guide the dose to be given.

It is not possible to replace fibrinogen to levels normally associated with delivery with FFP because the concentration of fibrinogen in FFP is less than 4 g/l. In addition, there is substantial delay between deciding to give FPP and/or cryoprecipitate and its infusion. This is because requesting FFP/cryoprecipitate from the laboratory, thawing it, issuing it and transporting it from the laboratory to the delivery suite usually takes around 60 min even with an efficient system. Fibrinogen concentrate (RiaSTAP® manufactured by CSL Behring, Marburg, Germany) can be used to rapidly replace fibrinogen to the pregnancy-related normal range [17] and will be used in this study. Anecdotal data suggest that fibrinogen concentrate may be useful as rescue therapy in managing severe hypofibrinogenaemia associated with massive PPH. In a number of case series, severe haemorrhage was clinically arrested or substantially improved when fibrinogen concentrate was used during severe and on-going bleeding [17-19].

A potential point-of-care surrogate test for the fibrinogen level is the Fibtem measured on the ROTEM® machine. The Fibtem assay gives results after 5 min (A5) and at the time of maximum clot firmness (MCF). Prospective data collected during major PPH in Cardiff have shown that the A5 and MCF are strongly correlated (r^2^ 0.93) but the A5 is available a median (IQR) 19 (13–24) min earlier than the MCF. The A5 is available on average 6 min after the start of the Fibtem assay. The A5 is between 1 and 2 mm lower than the MCF. The Fibtem A5 has been shown to correlate well with the laboratory-measured fibrinogen level during early PPH [20] and a result is available within 10–15 min after taking blood. The Fibtem assay has been used successfully to guide fibrinogen replacement with fibrinogen concentrate following complex cardiac surgery and was shown to have a large effect on bleeding and transfusion requirement [21].

In a Cardiff prospective observational study over a 12-month period of 346 analysable women experiencing a major PPH, 318 had a Fibtem performed and 332 had a Clauss fibrinogen (in press) (NB: the paper includes one more case than presented in this paper and hence the results are not identical). In this cohort the utility of Fibtem A5 and MCF to predict the need for red cell transfusion was investigated. For the need for any red cell transfusion, the ROC AUC (95% CI) for Fibtem A5 was 0.62 (0.55-0.69) and MCF was 0.62 (0.55-0.69), a result almost identical to that with the laboratory fibrinogen, 0.68 (0.61-0.75). Fibrinogen, Fibtem A5 and MCF had improved utility for predicting larger bleeds: for the need for 4 units of red blood cells the ROCs were 0.75 (0.64-0.87), 0.77 (0.67-0.87) and 0.78 (0.67-0.88) respectively. The results for the need for eight or more units of allogeneic products (red cells + FFP + platelets + cryoprecipitate) were 0.81 (0.70-0.92), 0.79 (0.67-0.91) and 0.79 (0.67-0.91) for fibrinogen, A5 and MCF respectively. This supports the potential use of Fibtem A5 or MCF instead of a laboratory fibrinogen level to guide treatment in this situation. Given that A5 and MCF give equivalent information and the A5 is available on average 19 min earlier than MCF, it allows earlier intervention during major PPH and hence is the preferred parameter to use for this study.

In the Cardiff prospective study there were 32 women with a Fibtem A5 below 16 mm (or a Clauss fibrinogen below 3 g/l) and on-going bleeding (>250 ml). Of these 27 (84%) required a red cell transfusion; mean (SD) number of units of red cells transfused was 4.1 (3.9). The mean (SD) number of units of allogeneic blood products was 8.2 (8.7). Of the 32 women, 7 also received between 3 and 7 g of fibrinogen concentrate as rescue haemostatic therapy.

Of the 288 women who had a Fibtem A5 of 16 mm or above or did not have on-going bleeding, and so would not have been randomised in the prospective study, 64 (22%) received a red cell transfusion, mean (SD) 0.55 (1.20 units/woman). The mean (SD) number of allogeneic units was 0.79 (2.19). The PPV (95% CI) for the need for a red cell transfusion of a Fibtem A5 below 16 mm in women with on-going bleeding was 84 (67–94)%. The NPV was 78 (73–82) %.

In the same study, of the 84 women with a Fibtem A5 of 23 mm or above, 16 (19%) received a red blood transfusion [median (range) 2 (2–5) units]. The mean (SD) number of units of red cells transfused was 0.44 (0.99) with a median (IQR) of 0 (0–0) units. The mean (SD) number of allogeneic units transfused was 0.58 (1.51) with a median (IQR) of 0 (0–0) units.

Although there is not a direct relationship between Fibtem and fibrinogen levels, in women experiencing major PPH, a Fibtem A5 of 16 mm is associated with a fibrinogen level below about 3 g/l and a Fibtem A5 of above about 23 mm with a fibrinogen above 4 g/l (prospective unpublished data from Cardiff and Huissoud 2009).

### Objective

The aim of this study is to investigate whether infusion of fibrinogen concentrate, based on the Fibtem A5 test, during a moderately severe PPH reduces the total number of allogeneic blood products transfused after study medication until discharged compared to placebo. The effect of fibrinogen on efficacy endpoints will be assessed as a secondary outcome.

## Methods and design

### Overview

This is a prospective, randomised, double-blind, placebo controlled trial. A total of 60 women will be included in the randomisation phase. The trial schema is shown in Figure 1.

**Figure 1 Fig1:**
[figure not shown]
Trial schema.

### Inclusion criteria

Age 18 years or over,Gestation ≥24 + 0 weeksWomen should have any one of the following either before delivery or within 12 h after delivery: haemorrhage of about 1500 ml and on-going bleeding without another complication or haemorrhage of about 1000 ml and on-going bleeding with any of:o Caesarean sectiono Uterine atonyo Placental abruptiono Placenta praeviao Cardiovascular instability (arterial blood pressure below 90 mm/Hg and heart rate greater than 100 bpm)o Clinical observation of microvascular oozing

### Exclusion criteria

Women who have documented that they do not want to participate in the study during the antenatal periodWomen declining infusion of red blood cells or blood componentsKnown inherited bleeding disorderPlacenta accreta diagnosed antenatallyWomen who have already received uterine brace sutures, uterine tamponade balloons, radiology intervention or hysterectomy before entering the studyClinical suspicion of amniotic fluid embolismSecondary postpartum haemorrhage (defined as abnormal bleeding starting between 24 h and 6 weeks after delivery).

### Sample size

On the basis of data prospectively collected in Cardiff in a study with the same entry criteria as this trial, the sample size was derived in the following way:

From a group of women with on-going bleeding (further bleeding of ≥250 ml after enrolment) and with a Fibtem A5 < 16 mm (representing women who would be the control/placebo group), the total number of allogeneic units (red cells + FFP + cryoprecipitate + platelets) transfused was positively skewed. The data were therefore transformed using the natural log (x + 1) transformation. This resulted in a more normal distribution with a mean [standard deviation (SD)] of 1.811 (1.004) on the log-transformed scale. Back-transforming this data gives a geometric mean of 5.12 units of allogeneic blood transfusions. Using the data from low-risk women with Fibtem A5 > 22 mm (representing what we would expect in the intervention group) then using the same transformation, the mean (SD) is 0.256 (0.539). Back-transforming gives a geometric mean of 0.30 units of allogeneic blood transfusions. This demonstrates a difference of 1.811-0.256 = 1.556 on the log-transformed scale.

A total of 60 patients can realistically be recruited. Therefore basing our sample size calculation on 27 per group (54 in total plus a 10% dropout), if the mean on the transformed scale in the intervention group is 1.036, this is the size of difference that we would be able to detect with power 80% at the two-sided 5% alpha level [22]. A transformed mean of 1.036 corresponds to a back-transformed ‘geometric mean’ of 1.81 allogeneic units. This is a 3.3 unit reduction, when measured as a simple difference on the original scale. The size of difference between control and intervention groups we might assume from this, when expressed on the log-transformed scale, is 1.811-1.036 = 0.775.

In the light of the difference found between the high- and low-risk groups (1.552), the assumption we are making for the new study still appears to be cautiously conservative. Thus we conclude that 27 individuals in each treatment arm (54 in total) would give 80% power to attain a difference of 3.3 total allogeneic units (0.775 on a log-transformed scale) at a conventional 5% alpha level. Assuming a 10% loss to follow-up, this will enable 60 women (30 per treatment group) to complete the trial and achieve the above numbers.

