**Figure 2 Fig2:**
[figure not shown]
Observational phase.

Blood will be taken for full blood count (FBC), coagulation screen and group and save/cross match and sent to the routine laboratory for analysis. These tests are part of standard care.At the same time as the routine blood tests, an extra 5-ml sample will be taken into a coagulation screen bottle and a Fibtem test will be performed on a ROTEM machine located in the delivery suite or obstetric theatre.A measurement will be made of the blood loss according to the procedures described below as soon as possible after study entry.

If the Fibtem A5 is less than 16 mm, the bleeding is on-going and the baby has been delivered, the woman will enter the interventional phase. If the Fibtem A5 is 16 mm or above further Fibtem assays may be performed after each 500 ml additional blood loss or for clinical concern. If any subsequent Fibtem falls below 16 mm the woman will enter the interventional phase (Figure 3).

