### Primary analysis

For those who enter the interventional phase of the study, the primary outcome will compare the total number of units of allogeneic products (red blood cells, FFP, cryoprecipitate, and platelets) transfused after study medication until discharge from hospital between women who received fibrinogen concentrate and placebo. A Poisson regression model will be used with due emphasis placed on confidence intervals for the between-arm comparisons with an investigation of site-level clustering. The primary analyses will also be repeated controlling for any baseline imbalances. While the main analyses will be based on ITT without imputation, we will undertake sensitivity analyses in order to estimate the effect of those randomised to fibrinogen but not receiving it using complier average causal effect (CACE) estimates, implemented in Stata using instrumental variable regression [24].

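### The sample size section claims 80% power for a 3.3-unit reduction, but 3.3 is a gap between back-transformed log means, not a difference in mean units

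*Protocol article*

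**What the plan says.** The Sample size section of the protocol article takes its control inputs from a Cardiff cohort and transforms total units x to ln(x + 1): "This resulted in a more normal distribution with a mean [standard deviation (SD)] of 1.811 (1.004) on the log-transformed scale". It sets the intervention mean at 1.036 on that scale, a difference of 0.775 that 27 women per group can detect "with power 80% at the two-sided 5% alpha level". The two means are back-transformed to 5.12 and 1.81 units and labelled geometric means. Of the gap between them the section says: "This is a 3.3 unit reduction, when measured as a simple difference on the original scale". Its conclusion is that 27 per arm "would give 80% power to attain a difference of 3.3 total allogeneic units (0.775 on a log-transformed scale").

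Two other places bear on this. The Background describes 32 Cardiff women who had a Fibtem A5 below 16 mm, or a Clauss fibrinogen below 3 g/l, and who kept bleeding: "The mean (SD) number of units of allogeneic blood products was 8.2 (8.7"). The Primary analysis section says of total units: "A Poisson regression model will be used".

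On who supplied the control inputs, the Sample size section specifies women with "further bleeding of ≥250 ml after enrolment". Entry to the interventional phase is described differently under Observational phase: "If the Fibtem A5 is less than 16 mm, the bleeding is on-going and the baby has been delivered".

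**The concern.** A simple difference on the original scale should mean a difference in average units transfused. The 3.3 is not that. With counts as skewed as these, the back-transformed log mean (5.12) lies well below the arithmetic mean (8.2 in the Background group), so a gap between two back-transformed means understates the change in mean units that the powered shift implies.

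The label matters because the primary model works on mean counts: a Poisson regression estimates a ratio of arithmetic means, not a difference in mean ln(x + 1). The article gives no power on that measure. Anyone who carries away 80% power for 3.3 units, and then sees a null result from the Poisson model, may conclude that a 3.3-unit benefit has been excluded when the trial was more likely to miss it than to find it.

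A second, smaller point concerns the same inputs. They come from women selected on bleeding that happened after enrolment, which cannot be known at randomisation.

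**Working it through.** **1. The plan's own figure.** Inputs from Sample size: difference 0.775, SD 1.004, 27 per arm, two-sided 5%.
- Standardised difference: 0.775 / 1.004 = 0.772.
- Noncentrality: 0.772 × √(27/2) = 2.84.
- Power: 79.5% by noncentral t (52 df), 81.0% by the normal approximation. 54 / 0.9 = 60.

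The log-scale calculation reproduces.

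**2. Where 3.3 comes from.** exp(1.811) − 1 = 5.12 and exp(1.036) − 1 = 1.82 (printed as 1.81). The gap is exp(1.811) − exp(1.036) = 3.30. As a ratio, the powered effect is exp(−0.775) = 0.46 in the geometric mean of units + 1.

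**3. What 0.775 means for mean units.** Assume the Background mean of 8.2 applies to the control arm. If every x + 1 shrinks by the factor 0.46, so does its mean: 9.2 × exp(−0.775) − 1 = 3.24. The fall is 8.2 − 3.24 = 4.96 units, about 60%. Treating x + 1 as exactly log-normal gives exp(1.811 + 1.004²/2) − 1 = 9.13 for control and 3.66 for intervention, a fall of 5.46. Neither is close to 3.3.

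**4. Power for a true 3.3-unit fall in the mean, 8.2 to 4.9.** With a negative binomial variance fitted to 8.2 (8.7):
- k = (8.7² − 8.2) / 8.2² = 67.49 / 67.24 = 1.004.
- SE of the log ratio = √[(1/8.2 + 1/4.9 + 2 × 1.004) / 27] = 0.294.
- z = ln(8.2/4.9) / 0.294 = 0.515 / 0.294 = 1.75.
- Power = Φ(1.75 − 1.96) = 42%.

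Other assumptions, same means, 27 per arm:

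| Assumption | Power |
|---|---|
| Log ratio, constant coefficient of variation (8.7/8.2) | 43% |
| Quasi-Poisson, variance/mean fixed at 8.7²/8.2 = 9.2 | 34% |
| Raw units, SD proportional to the mean | 39% |
| Raw units, common SD 8.7 | 28–29% |
| ln(x + 1), shift ln(9.2/5.9) = 0.444, SD 1.004 | 36–37% |

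Simulated negative binomial counts (20,000 runs) gave 33% for the log-scale t-test, 37% for a Welch test on units, 40% for quasi-Poisson and 46% for Poisson with robust standard errors. The last had a type I error of 6.9%.

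**5. Effect detectable with 80% power.** Under the negative binomial variance, ln(8.2/m) / SE(m) reaches 2.80 at m = 3.55, a fall of 4.65 units (57%). For 8.2 to 4.9, about 69 women per arm would be needed.

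**6. Plain Poisson, no overdispersion.** SE = √[(1/8.2 + 1/4.9) / 27] gives a nominal power of 99.7%. When the data are overdispersed as above, simulated rejection is about 85%, but the true type I error is about 52%, so this is not usable power.

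**7. Control inputs.** The source women had to bleed at least another 250 ml after enrolment. A randomised woman needs a low A5, current bleeding and a delivered baby, with no such later threshold. Women whose bleeding stopped soon after the test are therefore absent from the inputs but can be randomised.

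**The case against.** The best defence is that nothing in the power calculation is miscalculated. The 80% holds for 0.775 log units, both back-transformed means are called geometric, and 0.775 stands beside 3.3 in the conclusion. All of that stands. A reader might infer that the 80% itself is an arithmetic error; it is not. The fault is the unit claim attached to it and its mismatch with the primary model.

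It can also be objected that 42% is not the power of the planned model. That is right. The article names Poisson regression and no overdispersion correction, so the 42% belongs to a variance model supplied here.

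The 8.2 (8.7) group may not be the sample size group: it admits women on Clauss fibrinogen alone, and 7 of the 32 also received fibrinogen concentrate. The conversion to about 5 units is approximate as well, since shrinking every x + 1 by 0.46 would take women with zero units below zero. Both caveats stand, but they do not rescue the 3.3. With the log-normal control mean of 9.1 (SD 13.4) implied by the plan's log-scale inputs, power for a 3.3-unit fall in the mean is lower still: about 15 to 20% on mean-based tests and about 30% on the log scale.

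A reader might further infer that 60 women are too few for the effect the plan assumes. The figures do not establish that. Under the negative binomial variance, a fall from 8.2 to 3.24 has SE 0.30, z = 3.09 and power of about 87%. Simulated log-normal counts with the 0.775 shift gave 78% on the log scale, 70% for Poisson with robust standard errors and 63% for quasi-Poisson. The answer depends on the analysis and the distribution.

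Finally, it is tempting to put a number on the control selection. If 10 to 40% of randomised women behaved like the low-risk group in both arms, log-scale power would fall to between 68% and 36%. But no document gives that share, and assigning women with a low A5 the profile of women with an A5 above 22 mm is a severe assumption. Nor does the section contradict itself: it says that the source study shared the trial's entry criteria and then describes a subset of it.

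**Conclusion.** Wrong as written, in the unit claim and not in the log-scale calculation. Calling 3.3 a simple difference on the original scale is incorrect whichever variance model is used, because it is a difference of back-transformed ln(x + 1) means.

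The size of the discrepancy depends on taking 8.2 (8.7) as the control mean and SD. On that assumption the powered shift is a fall of roughly 5 mean units, about one and a half times the figure advertised. Power for a true 3.3-unit fall in the mean is about 42% with a negative binomial variance and about 28 to 46% across the overdispersed alternatives; none comes near 80%.

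The selection of control women on later bleeding is a real weakness in the inputs and probably makes the control mean too high for the women who will be randomised. Its effect on power cannot be determined from the documents.

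**What to change.** Keep 60 women and change the text of the Sample size section.

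- State the detectable effect as 0.775 on ln(x + 1), equivalently a ratio of 0.46 in the geometric mean of units + 1.
- Delete the description of 3.3 as a simple difference on the original scale, and the claim of 80% power for 3.3 units.
- Add the approximate detectable effect for a count model that allows for overdispersion, with its assumptions: about 4.7 to 5 mean units (57 to 60%) if the control mean is 8.2 (SD 8.7). State that power for a 3.3-unit fall in the mean is well below 80%.
- Recompute the control mean and SD from all cohort women with an A5 below 16 mm who were bleeding when tested, whatever they bled afterwards, and report the detectable difference that follows.

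The cost is recalculation on data the investigators already hold and a few reworded sentences. No additional women are needed. The price is a less favourable stated figure.
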